#### Performance Evaluation

In case of a lower-than-expected number of observed outcomes, or smaller differences than expected between those who experience the outcome and those who do not, we may revert from our 80:20 split to use cross-validation to measure performance. In that case, we will evaluate the algorithm using the leave-one-out cross-validation technique. We will implement this approach by leaving out one patient at a time (corresponding to potentially multiple observation periods to avoid fitting the model on data from the same patient as the model is being evaluated). The leave-one-out cross-validation technique facilitates cross-validation evaluation of the algorithm structure to assess its robustness to changes. This validation step will remake the algorithm for every patient left out of the algorithm development iteration. In short, this approach fits each algorithm using all available data except for (in our case) the data of one patient and then summarizes whether the algorithm predicts the correct classification of decompensation or nondecompensation for each observation period. This process is repeated over all available patients. For each τ, we will summarize the accuracy, false positives, and false negatives.

The resulting predicted probabilities of decompensation will then be translated into the easy-to-communicate AIDI, where there is a linear relationship between the risk score and the AIDI. At the conclusion of phase 3, the final COVID-19 DE detection performance of the AIDI will be evaluated using standard measures including sensitivity, specificity, and positive predictive value across a wide range of risk cutoff values. Overall, AIDI DE detection performance and lead time statistics will be examined across study populations as well as within subgroups. If necessary, to improve prediction accuracy, data may be stratified based on biological sex, race, ethnicity, or underlying clinical characteristics into subgroups to determine if there are differences in performance and detection lead times among the groups.

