**Methods:**

Overall, 200 participants will be enrolled. Inclusion criteria are patients in the US Department of Veterans Affairs health care system; “severe” COVID-19 infection during the acute phase, defined as requiring hospitalization, within 3-6 months before enrollment; aged ≥18 years; and having 1 of 6 prespecified chronic conditions. All participants will be instructed to use the MouthLab device to capture daily physiological data and complete monthly symptom surveys. Structured data collection tables will be developed to extract the clinical characteristics of those who experience decompensation events (DEs). The performance of the AIDI will depend on the magnitude of difference in physiological signals between those experiencing DEs and those who do not, as well as the time until a DE (ie, the closer to the event, the easier the prediction). Information about demographics, symptoms (Medical Research Council Dyspnea Scale and Post-COVID-19 Functional Status Scale), comorbidities, and other clinical characteristics will be tagged and added to the biomarker data. The resultant predicted probability of decompensation will be translated into the AIDI, where there will be a linear relationship between the risk score and the AIDI. To improve prediction accuracy, data may be stratified based on biological sex, race, ethnicity, or underlying clinical characteristics into subgroups to determine if there are differences in performance and detection lead times. Using appropriate algorithmic techniques, the study expects the model to have a sensitivity of >80% and a positive predicted value of >70%.

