#### Outcome Modeling

We will define the outcome as patients experiencing a DE within τ time units (DEτ). For different values of τ, we will deploy a series of more sophisticated models in order to explore the predictive ability of different approaches, as detailed below. We will split up the data into training and testing datasets based on the time of enrollment. We anticipate an 80:20 split; in other words, we will set aside 20% of the data to evaluate the model performance. For each τ, we will construct a training dataset consisting of multiple overlapping time segments for each patient, which we refer to as the observation period (eg, 2 weeks), and multiple nonoverlapping time segments leading up to the outcome for the patients that experience the outcome, one of which contains the outcome.

Second, we will explore several other machine learning algorithms, including classification trees, random forest, and boosting approaches, to understand whether these more flexible modeling approaches have an advantage over the logistic regression approach. The output of any of these approaches is a predicted probability of a DE occurring within the following τ days given observations of a fixed observation interval (eg, up to 30 previous measurements, or ~2 weeks). As stated earlier, the goal is to develop the AIDI to predict worsening health. The detailed analysis laid out above will allow us to understand the ability of early prediction, that is, the critical time frame just prior to decompensation during which the probability of hospitalization becomes increasingly predictive.

The initial exploratory analysis will inform the selection of proper features for the analysis. We will model the patient’s risk of hospitalization as a function of their physiological values, short-term changes in those values, changes from the baseline, etc. The initial exploratory analysis will inform features such as the appropriate time ranges (eg, should short-term changes be captured since the last reading or over the last 24 hours).

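### The validation method may be changed because DE/non-DE differences look small, and model choices are not tied to training data, so reported AIDI performance may be optimistic

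*Protocol article*

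**What the plan says.** Protocol article, Outcome Modeling: "We will split up the data into training and testing datasets based on the time of enrollment". It continues: "We anticipate an 80:20 split; in other words, we will set aside 20% of the data to evaluate the model performance".

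Protocol article, Performance Evaluation, gives two conditions for leaving that design. The first concerns event numbers: "In case of a lower-than-expected number of observed outcomes". The second concerns separation between the groups: "smaller differences than expected between those who experience the outcome and those who do not, we may revert from our 80:20 split". The fallback is cross-validation that omits one whole patient at a time and rebuilds the algorithm each time.

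On model choice, Outcome Modeling says: "The initial exploratory analysis will inform the selection of proper features for the analysis". The same exploratory work is to settle the time ranges over which changes are measured. Beyond logistic regression, "we will explore several other machine learning algorithms, including classification trees, random forest, and boosting approaches". The article does not say on which part of the data these steps are done.

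On reporting, results are summarised for each prediction window τ, and the final index is assessed by "sensitivity, specificity, and positive predictive value across a wide range of risk cutoff values". The abstract states an expectation of sensitivity above 80% and positive predictive value (PPV) above 70%, and it says: "The performance of the AIDI will depend on the magnitude of difference in physiological signals between those experiencing DEs and those who do not".

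**The concern.** The second condition makes the choice of validation method depend on the predictor-outcome relationship. Whether differences are smaller than hoped can be known only by comparing patients with and without a DE. By the abstract's own account, those differences drive performance, so a close proxy for the result helps to decide how the result is measured. The wording is permissive, and it gives no size for the expected difference, no time for the decision and no limit to the training patients. Weak separation is also no reason to prefer one validation method over another; a low event count is.

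Once the split is dropped, every patient serves both development and evaluation. The estimate is then honest only if everything learned from outcomes is relearned without the omitted patient. The exploratory selection of features and time ranges and the comparison of algorithms are not tied to the training part or to the fold. The study's stated aim is to develop and validate the AIDI, so the credibility of the performance estimate is its main product.

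**Working it through.** **Inputs from the article (Sample Size; Outcome Modeling; abstract).** 100 DEs wanted, 60% event rate, 168 completers, 15% dropout, 200 recruited, 80:20 split, expected sensitivity above 80%.

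**The plan's own figures.** 100 / 0.60 = 166.7, so 167 completers against 168 stated (168 × 0.60 = 100.8 DEs). 168 / 0.85 = 197.6, so 198 against 200 stated. Both reproduce closely and are not in dispute.

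**Size of the hold-out.** 0.20 × 100 = about 20 DEs, if DEs are spread evenly over enrolment time. Treating each DE as one independent trial, an observed sensitivity of 80% has these exact 95% intervals:
- 16 of 20: 56% to 94%
- 80 of 100 (all DEs, as in cross-validation): 71% to 87%

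A move to cross-validation because events are few is therefore reasonable in itself.

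**Effect of the switch alone.** Assume true sensitivity 70%. As a harsh stand-in for the trigger, suppose the split result S (20 DEs) is kept when above 80%, and otherwise an honest cross-validated result on all 100 DEs is reported.
- P(S > 80%) = P(X ≥ 17), with X ~ Binomial(20, 0.70), = 0.0716 + 0.0278 + 0.0068 + 0.0008 = 0.107.
- The cross-validated result shares the 20 DEs, so its mean given S is 0.2S + 0.8 × 0.70. The gain in the mean reported value is 0.8 × E[(S − 0.70); S > 0.80].
- That is 0.8 × (0.15 × 0.0716 + 0.20 × 0.0278 + 0.25 × 0.0068 + 0.30 × 0.0008) = 0.8 × 0.0182 = 0.0146.
- The mean reported sensitivity is thus about 71.5% instead of 70.0%; simulation gave the same.
- Simulated chance of reporting above 80%: 10.7% with the split alone, 0.9% with honest cross-validation alone, 11.2% with the switch.

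**Effect of choosing features on all data.** This is an illustrative simulation; apart from the 168 patients and 100 DEs, its settings are assumptions. There is one summary record per patient, 10 features are picked from 50, 100 or 200 candidates, the score is linear, and each setting has 200 runs. The weak signal is 0.3 SD on 5 features. Mean AUC:

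| Candidates | Signal | Leave-one-patient-out, features from all data | Leave-one-patient-out, features chosen in fold | 80:20, features from all data | 80:20, features from training data |
|---|---|---|---|---|---|
| 50 | none | 0.67 | 0.50 | 0.67 | 0.50 |
| 100 | none | 0.71 | 0.49 | 0.72 | 0.51 |
| 200 | none | 0.75 | 0.50 | 0.75 | 0.50 |
| 50 | weak | 0.72 | 0.59 | 0.71 | 0.57 |
| 100 | weak | 0.75 | 0.58 | 0.75 | 0.57 |
| 200 | weak | 0.78 | 0.56 | 0.78 | 0.56 |

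The inflation is about the same under either validation method. What matters is where the selection is done.

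**Effect of choosing the algorithm on the evaluation data.** Take four equally good algorithms (logistic regression and the three families named), each with true sensitivity 70%, and report the best. If their results were independent, the mean of the best is about 80% on 20 DEs and about 75% on 100 DEs. Algorithms scored on the same patients are positively correlated, so the real effect would be smaller.

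**The case against.** The article is a condensation, and a full protocol or analysis plan may say where selection takes place. Setting data aside to evaluate performance ordinarily implies that they are not used for selection. Rebuilding the algorithm for each omitted patient may include choosing features again, although the reference to algorithm structure leaves this open. Whole patients are left out, regularization is planned, and the differences that trigger the switch could be judged in the training data alone. All of this stands, and it limits the point. Regularization, however, restrains a fit; it does not correct for features already picked on the evaluation data. The outcome-dependent trigger is stated text, not silence.

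Four stronger readings are tempting, and the documents do not support them:
- A reader might infer that the best τ and the best cutoff will be picked. The article says results are summarised for each τ and across a wide range of cutoffs, and it names no selection. Multiplying algorithms by τ values and cutoffs to get a larger best-of-many figure would maximise over choices that the plan does not maximise over.
- A reader might infer that only the final fit is repeated in each fold. The text on rebuilding the algorithm does not say so.
- A reader might infer that performance will be optimistic. The article does not say that test data are used for selection.
- A reader might infer that the 80% and 70% figures decide whether the AIDI counts as validated. They are stated as expectations, with no pass/fail rule.

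**Conclusion.** The point holds in limited form. The firm defect is the trigger based on smaller differences: it depends on outcomes, is discretionary, and has no threshold, timing or restriction to training data. Its own effect is small if the cross-validation is honest: about 1.5 percentage points in mean sensitivity, under an assumed true value of 70%, 20 hold-out DEs out of 100, and one independent trial per DE. The larger risk is that features, time ranges or algorithm are chosen on data that also give the reported performance. In the simulation this raised AUC from about 0.50 to between 0.67 and 0.75 with no signal, and from 0.56–0.59 to 0.71–0.78 with a weak one. Those sizes rest on the assumed number of candidate features and a simple score; they show what is possible and are not estimates for this study. That risk also rests on the article's silence about where selection is done, so the supported conclusion is that reported performance may be optimistic. The wording should be settled before outcome data are analysed.

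**What to change.** - Delete the trigger based on smaller-than-expected differences.
- Allow a move to cross-validation only on a stated DE count, decided before any predictor-outcome analysis and before the test data are opened.
- State that feature, time-range and algorithm choice is done only within the 80% training data and that the held-out data are scored once. Under cross-validation, repeat these choices inside each left-out-patient fold.
- If a switch occurs, report both validations.
- Keep reporting for each τ and across cutoffs. If one τ and one cutoff are used to judge the expected sensitivity and PPV, fix them on training data.

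The cost is wording, more computing time and possibly slightly less favourable reported performance. No additional patients or data collection are needed.

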### Sample Size

To develop the AIDI algorithm, the study will collect longitudinal parameters that lead up to a DE with the MouthLab device. Because the actual multiparametric changes are unknown and are, in fact, the outcome of the study, the study aims to obtain as much data as possible from those who experience a DE. For this study, we estimate that 100 individual DEs would be sufficient to create a statistical algorithm to predict decompensation. The ultimate goal is to have the algorithm produce no false negatives (ie, if someone is at risk of decompensation while the algorithm says that they are not) and less than 10% false positives (ie, if someone is *not* at risk of decompensation while the algorithm says they are). That is, we do not want to miss any DEs at the cost of having some nonevents classified as being risky.

Al-Aly Z et al [11] observed that the risk and associated burden of pulmonary and extrapulmonary manifestations increase across the disease spectrum of acute COVID-19 infection (from nonhospitalized individuals to hospitalized individuals and then to those admitted to intensive care). The study implemented a comparative approach to examining postacute sequelae in individuals who are hospitalized with COVID-19 versus individuals with seasonal influenza (using a high-dimensional approach and through examination of prespecified outcomes). Results suggested that there is a substantially higher burden of a broad array of postacute sequelae in the individuals who are hospitalized with COVID-19, which provides features that differentiate post–COVID-19 condition (both in the magnitude of risk and the breadth of organ involvement) from postinfluenza viral syndrome [11]. A study by Mainous et al [2] demonstrated a hospitalization rate of 29.8% among survivors of “severe COVID-19.” Given that the AIDI study has defined “decompensation” more broadly than hospitalization alone, we anticipate higher decompensation rates among our study population. Conservatively estimating 1 DE per any participant, with an event rate of 60%, we would need 168 participants to complete the study in order to capture 100 DEs. Since we anticipate up to 15% dropout, we will aim to recruit 200 participants.

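### The leave-one-out fallback is credited with assessing robustness, which it cannot show, and pooling its predictions can bias performance downward when signal is weak

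*Protocol article*

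**What the plan says.** The main validation in the Protocol article (Outcome Modeling) is a split by time of enrollment: "We anticipate an 80:20 split; in other words, we will set aside 20% of the data to evaluate the model performance". Performance Evaluation adds a fallback for the case of fewer outcomes, or smaller differences between those with and without the outcome, than expected: "we may revert from our 80:20 split to use cross-validation to measure performance". The method for this fallback is then named: "we will evaluate the algorithm using the leave-one-out cross-validation technique". The unit is the patient: "We will implement this approach by leaving out one patient at a time". The plan then credits the technique with a second property, saying that it "facilitates cross-validation evaluation of the algorithm structure to assess its robustness to changes", and continues: "This validation step will remake the algorithm for every patient left out of the algorithm development iteration". The outputs named for this step are held-out results: "For each τ, we will summarize the accuracy, false positives, and false negatives".

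A separate paragraph of the same section plans a final evaluation of sensitivity, specificity and positive predictive value over a wide range of risk cutoffs. It does not say whether, under the fallback, these come from pooled leave-one-out predictions. Feature Engineering and Selection commits to regularization without giving its strength.

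**The concern.** There are two separate matters.

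The first is the claimed property. To learn whether an algorithm is robust to changes in the data, one has to change the data enough to matter. Removing one patient is the smallest possible patient-level change. Refits will agree closely whether or not the selected predictors would survive a new sample. The fallback also applies when events are few or differences small, which is when selection among features, time windows and algorithms is least stable.

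The second is pooling. Under leave-one-out, each patient's risk comes from a different model. A curve over cutoffs compares these risks as if they were on one scale. They are shifted slightly, and the shift depends on the left-out patient's own outcome: leaving out a DE patient makes the training event rate lower, and leaving out a non-DE patient makes it higher. When shrinkage is strong and the features carry little weight, this shift can dominate the ranking. At stake is a useful but weak index being shown as useless, or as worse than chance, because of the resampling scheme alone.

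**Working it through.** **Inputs.** Sample Size gives 168 completers, a 60% event rate, a target of 100 DEs, 15% dropout and 200 recruits. Results gives 204 enrolled. The simulations below use assumed data, because the document gives no effect sizes, feature count or penalty.

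**The plan's own figures.** The statement is "with an event rate of 60%, we would need 168 participants to complete the study in order to capture 100 DEs". 100/0.60 = 166.7, so 167, and 168 × 0.60 = 100.8. Recruitment: 168/0.85 = 197.6, so 198 against the stated 200. Both reproduce within rounding.

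**Step 1: overlap between refits.** Two leave-one-out training sets of size N − 1 share N − 2 patients, so the overlap is (N − 2)/(N − 1).

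| N | Overlap |
|---|---|
| 168 | 166/167 = 99.4% |
| 200 | 198/199 = 99.5% |
| 204 | 202/203 = 99.5% |

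For comparison, overlap is 75% for 5-fold and 88.9% for 10-fold. A bootstrap sample contains about 63% of the distinct patients.

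**Step 2: can agreement between refits reveal instability?** Two simulations with 168 patients and about 60% events measured the overlap (Jaccard index) of selected features.

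| Selection rule | Leave-one-out | 5-fold | Bootstrap | Fresh samples |
|---|---|---|---|---|
| L1 logistic, 50 features, 10 real at log-odds ratio ±0.3 | 0.87–0.91 | 0.38–0.47 | 0.24–0.38 | 0.11–0.34 |
| Top 5 of 60 features, no to moderate signal | 0.81–0.86 | not run | 0.14–0.21 | 0.05–0.12 |

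Leave-one-out refits agree with each other even when fresh samples would select largely different features.

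**Step 3: are the named outputs inflated?** In the top-5 simulation, for no, weak and moderate signal, leave-one-out accuracy was 0.53, 0.55 and 0.60. Independent-test accuracy was 0.55, 0.56 and 0.59, and apparent accuracy was 0.67, 0.69 and 0.70. The overlap does not inflate held-out accuracy.

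**Step 4: the pooling mechanism.** Take 168 patients with one record each and 100 with a DE.
- DE patient left out: training event rate 99/167 = 0.5928.
- Non-DE patient left out: training event rate 100/167 = 0.5988.

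At the limit of complete shrinkage the predicted risk is just this rate. Every DE patient then ranks 1/167 = 0.006 below every non-DE patient, and the pooled AUC is 0. With real features and light shrinkage, a shift of 0.006 is negligible. The question is what happens in between.

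**Step 5: size of the pooling bias** (ridge logistic, 168 patients, 50 features).

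One record per patient:
- *Fixed penalty, no signal, 60% and 30% events:* pooled leave-one-out AUC was 0.47–0.49 (light), 0.46 (moderate) and 0.30–0.33 (strong). Stratified 5-fold, summarised within folds, gave 0.49–0.50.
- *Fixed strong penalty, weak signal:* 0.35–0.39, against a true 0.54–0.55 and 5-fold 0.54–0.55.
- *Penalty tuned inside each refit, weak signal:* tuning chose heavy shrinkage in many datasets. Pooled leave-one-out averaged 0.19–0.43, against a true 0.54–0.55. Within-fold stratified 5-fold gave 0.49–0.55.
- *Penalty tuned, stronger signal:* 0.53–0.66 against a true 0.62–0.64.
- *Fixed penalty, 10 real features at ±0.3:* pooled against test AUC was 0.618/0.617 and 0.638/0.634 at penalties 1 and 30, and 0.580/0.637 at 300.

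Twelve segments per patient, closer to the plan's layout, 10 real features at ±0.3: 0.582/0.579, 0.581/0.574 and 0.564/0.566 at penalties 1, 30 and 300. It departed clearly only at 3000 (0.518/0.578).

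**The case against.** The strongest reply is that leave-one-out is only a conditional fallback and that its stated use is to measure performance. The plan reports correct classification, false positives and false negatives on held-out patients. It does not plan to compare refits and has no rule for declaring the index robust. A reader might infer that an unstable index would be reported as robust, or that reported accuracy would be too high. The documents support neither: no robustness verdict is planned, and Step 3 shows that an overfitted rule is exposed by its held-out accuracy. This part of the reply stands. What it leaves untouched is the sentence that assigns to the method a property it does not have.

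On pooling, it can be said that the document mentions no ROC curve or AUC, does not state that leave-one-out predictions are pooled across cutoffs, and gives no penalty strength. The bias also runs downward and is weaker with several observation periods per patient. All of this is correct, and it makes the second part of the point conditional. The claim that heavy shrinkage is a mere assumption stands less well: where the penalty was tuned and the signal weak, tuning itself often chose it, and small differences are one of the stated reasons for switching.

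Finally, patient-level leave-one-out is a legitimate choice when events are few. It keeps nearly all events in training and prevents leakage between periods of one patient. The second advantage is shared by any patient-level scheme. The first is real but modest against 80–90% of patients in training. Details such as the number of repeats may properly sit in a document not shown, and their absence is not criticised here.

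**Conclusion.** The point holds in limited form, as a cheap improvement. Refits that share 99.4% to 99.5% of patients cannot assess robustness to changes, and this part needs only the arithmetic in Step 1. Leave-one-out remains able to estimate held-out performance.

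The pooling bias is conditional on three things: the fallback is invoked, predictions are pooled across cutoffs, and the models are shrunk heavily while signal is weak. Under those conditions pooled discrimination can fall below chance although the index has some real predictive value. With stronger signal or light shrinkage the bias is small, and with several periods per patient it needs a heavier penalty to appear. The direction follows from Step 4. The sizes in Step 5 are illustrative, and most come from one record per patient. The 80:20 split by enrollment time, which is the main plan, is not affected.

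**What to change.** In Performance Evaluation:
- Make the fallback repeated patient-level 5- or 10-fold cross-validation, stratified by whether the patient had a DE (for example 20 repeats), or a patient-level bootstrap with optimism correction.
- Repeat feature selection and tuning inside each resample.
- Summarise discrimination within folds. Stratifying keeps training event rates nearly equal, and comparing only patients scored by the same model removes the shift in Step 4.
- Report how often each predictor and each algorithm is selected across resamples, and present that as the stability result.
- Delete the sentence that says leave-one-out assesses robustness.

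The cost is wording. With 20 repeats, computing is 5 × 20 = 100 or 10 × 20 = 200 refits, against 168 to 204 for leave-one-out. No new data are needed. The small downside is that each fold trains on 80% to 90% of patients, so estimated performance is slightly pessimistic.

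### The leave-one-patient-out fallback scores each observation period, so it cannot show how many decompensation events are missed, and its accuracy figure says little

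*Protocol article*

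**What the plan says.** Under Outcome Modeling, the label is a DE within a horizon τ, which takes several values and is not fixed. The data for fitting are "a training dataset consisting of multiple overlapping time segments for each patient", for example of 2 weeks, and the protocol calls these observation periods. The same sentence adds "multiple nonoverlapping time segments leading up to the outcome for the patients that experience the outcome, one of which contains the outcome". The main evaluation is a 20% hold-out by time of enrollment.

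Under Performance Evaluation, the plan may switch to leave-one-out cross-validation if outcomes are fewer, or group differences smaller, than expected. One whole patient is left out at a time, and the result is whether the algorithm "predicts the correct classification of decompensation or nondecompensation for each observation period". The summary follows: "For each τ, we will summarize the accuracy, false positives, and false negatives". The final evaluation of the index uses "standard measures including sensitivity, specificity, and positive predictive value across a wide range of risk cutoff values", together with lead-time statistics. The counting unit for that final step, and for the hold-out, is not given.

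Under Sample Size, the target is 100 individual DEs. The stated aim is that no DE is missed, at the price of some false alarms. The Abstract expects sensitivity above 80% and positive predictive value (PPV) above 70%.

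**The concern.** The aim is stated in events, while the only scoring unit that the article names is the observation period. These are different quantities. If several periods precede one DE, a period-level error rate mixes two situations that differ clinically: a DE flagged on some days and not on others, and a DE never flagged at all. Only the second is a missed event.

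Two further effects come with the unit. Most periods of most patients are negative, so overall accuracy is high whatever the model does. And the periods before one DE resemble each other, so the number of periods overstates the amount of independent information. Leaving out whole patients prevents leakage into the fit, but it does not make the scored periods independent. The fallback is meant partly for the case of few events, which is when the number of events, and not of periods, limits what can be learned.

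**Working it through.** **The plan's own figure.** 100 DEs / 0.60 = 166.7, so 167 completers (stated: 168; 168 × 0.60 = 100.8 DEs). Allowing 15% dropout, 168 / 0.85 = 197.6, so 198 (stated: 200). The sample size reproduces to within rounding. The article gives no figure for accuracy or interval width to reproduce.

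**Inputs.** From the protocol: 168 completers, 100 DEs with one per affected patient, 6 months of follow-up (taken as 182 days), and a look-back of about 2 weeks (taken as 14 days). Assumed, because not stated: one window per day, τ from 1 to 30 days, and the correlation ρ between periods of the same DE.

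**1. Can a period-level sensitivity show missed DEs?** At τ=7, each DE has 7 positive periods, so 100 DEs give 700. A sensitivity of 80% means 560 flagged periods. Two patterns give this total:
- every DE flagged in 560 / 100 = 5.6 of its 7 periods on average: 0 DEs missed;
- 80 DEs flagged in all 7 periods (80 × 7 = 560) and 20 never flagged: 20 DEs missed.

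The same holds at τ=14 (80% of 1,400 = 1,120 = 80 × 14).

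**2. Accuracy of a rule that never alerts.** Periods = 168 × (182 − 14) = 28,224. Positive periods = 100 × τ. Accuracy = 1 − positive share. As a variant, follow-up ends at the DE, at mid-study on average: 68 × 168 + 100 × 84 = 19,824 periods.

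| τ (days) | positive periods | accuracy, full follow-up | accuracy, follow-up ends at DE |
|---|---|---|---|
| 1 | 100 | 99.6% | 99.5% |
| 7 | 700 | 97.5% | 96.5% |
| 14 | 1,400 | 95.0% | 92.9% |
| 30 | 3,000 | 89.4% | 84.9% |

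Sensitivity is 0 in every row. Overlap is not the cause: with nonoverlapping 14-day windows there are 168 × 12 = 2,016 periods, of which 100 are positive, and accuracy is again 1 − 100/2,016 = 95.0%. The cause is that positive periods are rare. With one result per patient, a rule that always names the commoner class scores only about 60%.

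**3. Interval width if periods were treated as independent.** 95% half-width = 1.96 × √(0.80 × 0.20 / n).
- n = 100 DEs: ±7.8 points.
- n = 700 periods (τ=7): ±3.0 points. n = 1,400 periods (τ=14): ±2.1 points.
- If all periods of a DE agree (ρ=1), the interval is too narrow by √7 = 2.6 or √14 = 3.7.
- With design effect 1 + (τ − 1)ρ at ρ=0.5, the factors are √4 = 2.0 and √7.5 = 2.7.

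For a 20% share of 100 DEs, n = 20 gives ±17.5 points per DE.

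**4. The low-event case that triggers the fallback.** As an illustration, take the 29.8% hospitalization rate cited under Sample Size: 0.298 × 168 ≈ 50 DEs. Per DE the half-width is ±11.1 points. Counting 50 × 14 = 700 periods as independent would give ±3.0.

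**The case against.** Much of the case on the other side stands.

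- **Scope.** The per-period wording belongs to the fallback. A reader might infer that the hold-out is scored in the same way; the article does not say so.
- **Overlap.** It is stated for the training data, and the segments leading up to the outcome are called nonoverlapping. In leave-one-out every patient's periods serve as training data in the other folds, so scoring the same overlapping periods is the natural reading, but it is not spelled out. If each DE had only one positive period, per-period and per-DE sensitivity would coincide. The multiplicities of 7 and 14 are therefore conditional. The accuracy result does not depend on them.
- **Overstated precision.** A reader might infer that the reported precision will be too good. The documents do not support this. No interval or variance method is stated, and one may stand in an analysis plan that is not shown. Repeated counting does not by itself bias a period-level point estimate.
- **PPV.** If precision is read as PPV, the per-period unit works the other way. At sensitivity 0.80 and specificity 0.90, PPV is 0.8 × 0.0496 / (0.8 × 0.0496 + 0.1 × 0.9504) = 29% at the τ=14 period prevalence, against 0.48 / (0.48 + 0.04) = 92% at the 60% patient-level rate.
- **Accuracy as the headline.** It is not. Sensitivity, specificity, PPV and lead time are planned too, and a rule that never alerts would be exposed at once by its false negatives.

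What these points do not answer is the mismatch of unit. The fallback's false negatives are missed periods, while the aim concerns missed DEs, and no sentence says that DEs will be counted.

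**Conclusion.** The point holds in a limited form. Where the fallback is used, its stated tally cannot test the study's aim: at 80% per-period sensitivity the number of missed DEs can be anything from 0 to 20 in the two patterns shown. Per-period accuracy is close to uninformative for short horizons: about 97.5% at τ=7 and 95.0% at τ=14 for a rule that detects nothing, and 92.9% to 96.5% if follow-up ends at the DE. Too narrow an interval (2.0- to 2.7-fold at ρ=0.5, up to 2.6- to 3.7-fold at ρ=1) is a risk if periods are treated as independent, not an error found in the text.

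The accuracy figures rest on 168 completers, 100 DEs, 182 days, a 14-day look-back and the assumed τ. The missed-DE and interval figures also need daily windows with several positive periods per DE. The absence of a unit for the hold-out is a matter to settle, not a defect shown.

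**What to change.** State the unit of scoring once, for both the hold-out and the leave-one-out fallback:

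- sensitivity as the share of DEs with at least one alert in the τ days before onset;
- PPV per alert episode, consecutive alerts counting as one episode;
- false alerts per patient-month;
- 95% confidence intervals from a bootstrap that resamples whole patients;
- no use of per-period accuracy as a summary of performance.

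The first and third measures must be reported together. With 7 independent periods per DE, a rule that alerts in 30% of them would still catch 1 − 0.7⁷ = 92% of DEs, so event sensitivity alone would reward frequent alerting.

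The cost is a paragraph of text and modest programming; no new data are needed. The intervals will be wider: about ±7.8 points for 100 DEs and ±17.5 for 20 DEs at 80% sensitivity.
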